#### **11.6. Expectedness**

Expectedness will be determined according to the approved RSI, i.e. Summary of Product Characteristics.

#### **11.7. SUSAR Reporting**

In collaboration with the PC-CTU, CTRG and DMEC, the Trial Management group will report all SUSARs to

the Competent Authorities (MHRA in the UK), the Research Ethics Committee concerned and Host NHS Trusts.

All SUSARs will be reported electronically to the MHRA within the timelines defined in the Medicines for Human Use (Clinical Trials) Regulations 2004 (as amended) using the following e-SUSAR reporting link via the MHRA website: <https://esusar.mhra.gov.uk/>

To use the e-SUSAR link, a copy of the MHRA approval letter for a new trial should be sent to the Sponsor so that they can log the trial on to the e-SUSAR system that they maintain. The Sponsor will then send the CI, and anyone else that has been nominated, the log-in password and details for them to view the trial and report SUSARs directly on to the system.

A fatal or life-threatening SUSAR is reported as soon as possible to the MHRA, the competent authorities of any EEA State other than the United Kingdom in which the trial is being conducted, and the relevant Ethics Committee not later than 7 days after the Sponsor was first aware of the reaction. Any additional relevant information should be reported within 8 days of the initial report.

A SUSAR which is not fatal or life-threatening is reported as soon as possible and in any event not later than 15 days after the PC-CTU is first aware of the reaction.

The Trial Management group will also inform all members of the Research Team concerned of relevant information about SUSARs that could adversely affect the safety of participants.

Further details are available at <https://esusar.mhra.gov.uk/about/>.

### **11.8. Development Safety Update Reports**

In addition to the expedited reporting above, the CI shall submit once a year, throughout the clinical trial within 60 days of the date of the anniversary of the CTA or on request, a Developmental Safety Update Report to the Competent Authority (MHRA in the UK), Ethics Committee, Host NHS Trust and sponsor in line with PC-CTU\_SOP\_TM119 "Pharmacovigilance".

If approved under the notification scheme, the HRA Annual Progress Report (APR) form should be used as a template for the DSUR, and should include a list of all SARs in Section 6. The cover letter must state that this is an APR in lieu of a full DSUR, and include the EudraCT number and CTA reference number.

For assessment of SARs in the DSUR, the RSI that was approved at **the start of the safety reporting period** will be used. When there has been approved changes to the RSI by substantial amendment during the reporting period, the RSI used for the DSUR will differ to the RSI used to assess expectedness at the time of SAR occurrence for SARs which require expedited reporting.

## **12. STATISTICS**

### **12.1. Statistical Analysis Plan (SAP)**

The statistical aspects of the study are summarised here with details fully described in a statistical analysis plan. The SAP will be finalised before any analysis takes place.

## 12.2. Description of Statistical Methods

In accordance with CONSORT guidelines, we will record and report participant flow. Descriptive statistics of recruitment, drop-out, and completeness of interventions will be provided. Baseline variables will be presented by randomised group using frequencies (with percentages) for binary and categorical variables and means (and standard deviations) or medians (with lower and upper quartiles) for continuous variables. There will be no tests of statistical significance nor confidence intervals for differences between groups on any baseline variables.

The primary analysis will be on an intention-to-treat basis. That is, after randomisation, participants will be analysed according to their allocated treatment group irrespective of what treatment they actually receive. The primary outcome will be analysed using a survival analysis method, such as Cox proportional-hazards model, adjusting for practices. Results will be presented as hazard ratios with 95% confidence intervals and associated two-sided P-values. To test the robustness of the result, a sensitivity analysis will be carried out, using the same method, adjusting the following pre-specified baseline prognostic factors: diastolic and/or systolic blood pressure above or below NICE target, type II diabetes and coronary artery disease.

Same approach will be repeated for individual components of the primary composite endpoint and all-cause mortality as secondary analyses. Analyses for other outcomes will be carried out using multiple log-binomial regression models for binary data and linear mixed effect model for continuous data collected over time.

Assumption of proportional hazards will be examined and if any of the assumptions were violated, a suitable alternative survival method will be considered. Similarly, alternative methods will be considered if any violation of assumptions is detected in any of the aforementioned methods for other outcomes.

Adverse effects will be tabulated according to randomised group assignments and the proportions will be compared using Fisher's exact test.

A full detailed analysis plan, including approach of handling missing data, subgroup analyses, and sensitivity analyses, and a plan for interim analysis will be prepared before the final datalock and analysis by a statistician who is independent from the study. All analyses will be performed by the trial statistician and validated by a separate statistician.

## 12.3. Sample Size Determination

A UK representative spread of practices will be achieved by stratifying practice postcode location into quartiles of Townsend Deprivation Score and selecting practices that agree to take part sequentially until each deprivation quartile practice target is reached. This strategy will most probably ensure that populations selected will also be representative for ethnicity but the sequential practice selection strategy will be examined after ten practices have been selected for each deprivation quartile to ensure practices serving high proportions of ethnic minorities are included in the final five places, if this has not already occurred in the earlier selections.

The estimate for the cardiovascular (CV) event rate (defined by hospitalisation for coronary heart disease, heart failure, ischemic stroke and peripheral arterial disease) and total mortality rate in patients with CKD 3b (eGFR 30-44 ml/min/1.73m^2) being 11.29 and 4.76 per 100 person years respectively gives a combined

event rate of 16.05 per 100 person years [5]. In those with eGFR in the range 45-50 ml/min/1.73m^2, the event rate is conservatively estimated to be 0.667 times as high (10.7 events per 100 person years[76] and we assume half the participants will fall in this range giving an overall event rate of 13.4 events per 100 person years. To detect a 20% relative risk reduction in death or cardiovascular events within 3 years in the intervention group as compared with the control group (i.e. hazard ratio=0.8) with an anticipated treatment withdrawal rate of 13% (which gives a diluted estimated treatment effect = 0.84) and a two sided significance of 0.05, 1511 participants per group (3022 total) are required at 80% power and assuming 10% attrition rate.

We have decided to power the trial conservatively on a 20% risk reduction since this proposed treatment effect is around half the risk reduction observed in the ARA mild heart failure trial (EMPHASIS). The estimated hazard ratio in the EMPHASIS eplerenone versus placebo mild heart failure trial (only mildly symptomatic patients were included) were 0.63 (CI 0.54-0.74, p<0.001) for the composite endpoint of death from CV causes or hospitalisation for heart failure at the median follow up of 21 months. The conservative upper CI for the treatment effect was 26% reduction. The placebo CV event rate in EMPHASIS trial was similar to observational data on CV events in CKD 3b patients [5].

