| Metabolism and nutrition disorders                                  | 30 (7.7) 38               | 37 (3.8) 42              | 67 (4.9) 80         |
| Musculoskeletal and connective tissue disorders                     | 32 (8.2) 41               | 52 (5.3) 73              | 84 (6.1) 114        |
| Neoplasms benign, malignant and unspecified (incl cysts and polyps) | 15 (3.9) 25               | 31 (3.2) 33              | 46 (3.4) 58         |
| Nervous system disorders                                            | 41 (10.6) 57              | 76 (7.7) 96              | 117 (8.5) 153       |
| Psychiatric disorders                                               | 4 (1.0) 4                 | 8 (0.8) 10               | 12 (0.9) 14         |
| Renal and urinary disorders                                         | 23 (5.9) 25               | 47 (4.8) 58              | 70 (5.1) 83         |
| Reproductive system and breast disorders                            | 25 (6.4) 29               | 7 (0.7) 9                | 32 (2.3) 38         |

| Number of participants (%) number of events     | Spironolactone
(N=388) | Standard Care
(N=984) | Overall
(N=1372) |
|-------------------------------------------------|---------------------------|--------------------------|---------------------|
| Respiratory, thoracic and mediastinal disorders | 14 (3.6) 17               | 33 (3.4) 44              | 47 (3.4) 61         |
| Skin and subcutaneous tissue disorders          | 8 (2.1) 9                 | 12 (1.2) 13              | 20 (1.5) 22         |
| Social circumstances                            | 0 (0.0) 0                 | 1 (0.1) 1                | 1 (0.1) 1           |
| Surgical and medical procedures                 | 21 (5.4) 23               | 38 (3.9) 43              | 59 (4.3) 66         |
| Vascular disorders                              | 33 (8.5) 37               | 65 (6.6) 75              | 98 (7.1) 112        |
| Missing                                         | 0 (0.0) 0                 | 1 (0.1) 1                | 1 (0.1) 1           |

**Supplementary Table 2.** Summary statistics and the hazard ratio for the post hoc analysis based on a per-protocol principle and an on-treatment population

|                                                                                                                                               | Spironolactone
(N=677) | Standard Care
(N=695) | Hazard Ratio
[95 CI]† | P-value‡ |

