## 2.4 SAMPLE SIZE

The estimate for the cardiovascular (CV) event rate (defined by hospitalisation for coronary heart disease, heart failure, ischemic stroke and peripheral arterial disease) and total mortality rate in patients with CKD 3b (eGFR 30-44 ml/min/1.73m^2) being 11.29 and 4.76 per 100 person years respectively gives a combined event rate of 16.05 per 100 person years. In those with eGFR in the range 45-50 ml/min/1.73m^2, the event rate is conservatively estimated to be 0.667 times as high (10.7 events per 100 person years) and we assume half the participants will fall in this range giving an overall event rate of 13.4 events per 100 person years. To detect a 20% relative risk reduction in death or cardiovascular events within 3 years in the intervention group as compared with the control group (i.e. hazard ratio=0.8) with a two sided significance of 0.05, 1455 participants per arm are required seeking 90% power and assuming 10% drop out rate per year.

We have decided to power the trial conservatively on a 20% risk reduction since this proposed treatment effect is around half the risk reduction observed in the ARA mild heart failure trial (EMPHASIS). The estimated hazard ratio in the EMPHASIS eplerenone versus placebo mild heart failure trial (only mildly symptomatic patients were included) were 0.63 (CI 0.54-0.74, p<0.001) for the composite endpoint of death from CV causes or hospitalisation for heart failure at the median follow up of 21 months. The conservative upper CI for the treatment effect was 26% reduction. The placebo CV event rate in EMPHASIS trial was similar to observational data on CV events in CKD 3b patients.

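### Protocol 12.3 and SAP 2.4 give two different, undeclared sample-size calculations; the protocol's diluted effect of 0.84 does not fit its own 13% and N, and the SAP's 10% drop-out per year does not fit its 1455 at 90% power

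*Combined protocol and SAP*

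**What the plan says.** Protocol 12.3 (V8.0) takes a control rate "giving an overall event rate of 13.4 events per 100 person years" and a target hazard ratio of 0.80 over 3 years. It dilutes that effect "with an anticipated treatment withdrawal rate of 13% (which gives a diluted estimated treatment effect = 0.84" and concludes that "1511 participants per group (3022 total) are required at 80% power and assuming 10% attrition rate". Neither the 13% nor the 10% has a time unit, and the scale of the dilution is not given. The synopsis repeats the total of 3022.

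SAP 2.4 (V2.0, December 2022) uses the same event rate, the same hazard ratio and the same significance level, but states that "1455 participants per arm are required seeking 90% power and assuming 10% drop out rate per year". It has no treatment-withdrawal dilution.

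Protocol 12.1 says that the SAP gives the full description of what the protocol summarises. SAP section 11 names peripheral artery disease as the only departure from the protocol, and SAP section 10 is empty. Both documents specify an intention-to-treat primary analysis.

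**The concern.** The two paragraphs share their starting inputs but differ in sample size, power, the effect that is powered and the attrition assumption. A reader cannot tell which is the design basis. Each also contains a figure that does not fit the rest of its own paragraph. In the protocol, 13% withdrawal does not turn 0.80 into 0.84. In the SAP, 10% lost every year leaves too few events for 90% power with 1455 per arm.

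At stake is how the primary result is read. A non-significant hazard ratio will be set against the stated power. Someone who takes 0.84 at 80% from the protocol, or 0.80 at 90% from the SAP, credits the design with more information than those printed inputs give.

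**Working it through.** **Inputs** (protocol 12.3 and SAP 2.4): control hazard 0.134 per year, 3 years of follow-up, 1:1 allocation, two-sided 0.05, hazard ratio (HR) 0.80 before dilution. Event times are taken as exponential.

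**Formulas**
- Events needed (Schoenfeld): D = 4(1.960 + z)² / (ln HR)², with z = 0.842 for 80% power and 1.282 for 90%.
- Power with D events: Φ(|ln HR|·√D/2 − 1.960).
- Event probability without loss: 1 − exp(−3λ). With exponential loss at rate g: λ/(λ+g) × [1 − exp(−3(λ+g))].

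**1. The protocol's own figure**
- Dilution on the log scale: 0.80^0.87 = 0.8235. Linear dilution: 0.87 × 0.80 + 0.13 = 0.826.
- At 0.8235: D = 31.40/0.03769 = 833. Event probabilities are 0.3310 and 0.2818, sum 0.6129. 833/0.6129 = 1359 per group, and 1359/0.9 = 1510, against 1511 stated (1509 to 1512 depending on rounding). Power at 1511 is 80.0%.
- At 0.826, power at 1511 is 78.8%.

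So N follows from HR 0.80, 13% withdrawal and 10% attrition.

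**2. The protocol at the printed 0.84**
- Withdrawal needed to reach 0.84: linear, 0.04/0.20 = 20%; log scale, 1 − ln 0.84/ln 0.80 = 22%.
- Events needed for 80%: 31.40/0.03040 = 1033.
- Events expected: 1511 × 0.9 × (0.3310 + 0.2866) = 840.
- Power: Φ(0.1744 × √840/2 − 1.960) = 71.4%. It is 74% if the 10% is lost gradually over 3 years and 70% if 10% is lost each year.
- Needed for 80%: 1033/0.6176/0.9 ≈ 1858 per group.

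**3. The SAP as printed (HR 0.80, 10% lost per year, g = −ln 0.9 = 0.1054)**
- Events needed for 90%: 42.03/0.04979 = 844.
- Event probabilities 0.2868 and 0.2378, sum 0.5246. Expected: 1455 × 0.5246 = 763.
- Power: Φ(0.2231 × √763/2 − 1.960) = 86.9%. Needed for 90%: 844/0.5246 ≈ 1609 per arm.

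**4. The SAP with 10% lost over all 3 years (g = 0.1054/3 = 0.0351)**
- Sum of event probabilities 0.5770; 844/0.5770 ≈ 1463 per arm against 1455 stated; power 89.8%.

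**5. The SAP's 1455 per arm (2910 in total) at the protocol's diluted 0.8235**

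| 10% lost | Power |
|---|---|
| each year | 77% |
| over 3 years, taken as 0.9 × N | 79% |
| over 3 years, spread evenly | 81% |

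**6. Context only.** Supplementary Table 2 shows 677 + 695 = 1372 participants. At the planned event rate, with 10% lost, 686 × 0.9 × 0.6060 = 374 events are expected at HR 0.80, which gives 58% power. At 0.8235 it is 47%.

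**The case against.** The strongest reply is that the protocol's sample size is sound, and this stands. Its 1511 comes out almost exactly from HR 0.80, 13% and 10%, so the 71% follows from the printed 0.84 and is not evidence of a shortfall in N.

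Nor can the documents show which number is the slip. If 13% were a yearly rate, about 18% of person-time would be off treatment, and the diluted hazard ratio would be 0.833 (log scale) to 0.837 (linear), close to 0.84. If events were counted as rate × 3 years, ignoring depletion of those at risk, 0.84 gives about 1551 per group and 79% power at 1511. If 0.84 were a 3-year risk ratio, it would equal a hazard ratio of about 0.81, with power near 86%. These readings need a time unit, a rougher method or an effect scale that the text does not state. They are a reason to ask the sponsor for the method and not to impose 0.824 as the right number.

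The SAP gap is small, 87% against 90%, and probably lies in the words on drop-out per year. The 95% confidence interval, which both documents already require, will show what effects the data exclude whatever the planned power was. These replies limit the seriousness of the point. They do not explain why two calculations coexist, or why the SAP leaves out the dilution under an intention-to-treat analysis.

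**Conclusion.** The point holds, at moderate severity. Two incompatible calculations stand in the current documents without acknowledgement. In the protocol the figure that does not fit is 0.84: read as a hazard ratio it gives about 71% power at 3022, against 80% at 0.8235. In the SAP it is the yearly drop-out: about 87% power as printed, against 90% claimed. Without the dilution the SAP also claims 90% where the protocol's diluted effect would give 77-81%.

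These figures rest on exponential event times, the Schoenfeld approximation and 3 full years of follow-up. They also take the protocol's 13% as a total over the trial and its 10% as a proportion removed from N.

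A reader might infer more: that neither sample size can be reproduced, or that 1511 was too small for the planned withdrawal. The documents do not support that, because 1511 reproduces and 1455 reproduces under a 3-year drop-out. A reader might also judge the plan by the events in Supplementary Table 2. The row without peripheral arterial disease is a post hoc analysis of a different endpoint, and its event count shows no error in the plan. The lower power with 1372 participants likewise reflects the number randomised and not a mistake in either calculation.

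**What to change.** - Use one calculation in protocol 12.3 and SAP 2.4.
- Protocol: reconcile 0.84 with the 13% and N. Either restate the diluted hazard ratio as about 0.82-0.83, or keep 0.84 and state about 71% power. In both cases give the scale of the dilution and the time units of the withdrawal and attrition rates.
- SAP: preferably replace its figures with the protocol's reconciled ones. Otherwise change the drop-out to 10% over 3 years, or restate the power as about 87%. Carry the withdrawal dilution in either case, and restate the power at the diluted effect (77-81% for 1455 per arm).
- List any remaining difference in SAP section 11.
- Optionally, add the power for the 1372 randomised at the planned event rate, labelled as context.

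The cost is wording in two paragraphs and one line in section 11. The protocol keeps its 80% if the hazard ratio is what gets corrected; the SAP's claim falls below 90% once the dilution is carried. No participants, endpoints, models or estimates change.

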#### **12.4. Analysis Populations**

The primary analysis will be carried out on all randomised participants, on an Intention to treat (ITT) basis, assuming non-informative censoring for those withdrawn or lost to follow-up. Based in the ITT principle, participants who are withdrawn from treatment (e.g. for safety reasons) but consent to continue follow-up will be included in the ITT analysis. Participants who are withdrawn or lost to follow-up will be censored at the date of withdrawal or date of last follow-up, respectively. All participants will be analysed in the groups to which they were allocated, regardless of treatment compliance.

The safety population will include all participants who received the study medication.

#### **12.5. Decision Points**

There will be no interim analysis performed to assess treatment efficacy. The statisticians who prepares the DMEC reports and the DMEC assess the closed session reports with treatment allocation being blinded. All results of the closed report will only be available to the trial statisticians and the DMEC.

#### **12.6. Stopping Rules**

A formal futility analysis will be performed and fully reviewed by the DMEC.

#### **12.7. The Level of Statistical Significance**

5% significance level (2-sided)

#### **12.8. Procedure for Accounting for Missing, Unused, and Spurious Data.**

The missing at random assumption will be tested as far as is possible by analysing each baseline covariate in a regression model to determine which if any are associated with missingness.

All baseline covariates are expected to be observed. Baseline values will be summarised for those who did

and did not complete follow up measurements to describe any characteristics related to missingness that are able to be observed.

We will be analysing our data using an intention to treat analysis. All randomised patients will be included in the analysis, assuming non-informative censoring for those withdrawn from the study or lost to follow-up for the primary analysis.

During statistical data review and analysis, any anomalies in the data will be investigated and discussed with the trial management team. The data investigation will be broad and flexible and focus on variability of the data, consistency, dispersion, outliers, inliers, relationships between variables and relationships over time. The statistical data review will be fully documented with all the output dated. If fraud is proved, fraudulent data will be removed from the analysis.

### **12.9. Procedures for Reporting any Deviation(s) from the Original Statistical Plan**

We do not anticipate any major deviation from the Statistical Analysis Plan. However, provision for alternative methods and changes to analyses will be included in the Statistical Analysis Plan as specified in PC-CTU\_SOP\_ST104 "Statistical Report".

### **12.10. Health Economics Analysis**

A health economic analysis will be integrated into the trial.

*Research Question:* What is the cost-effectiveness of adding an ARA to usual care in CKD3b?

*Data collection:* The cost analysis will adopt an NHS perspective. Data on health care resource use will be collected from all trial patients, including all relevant hospital and GP consultations, medications, referrals, tests and equipment. Protocol-driven costs will be omitted. Where possible data on resource utilisation will be collected from electronic patient records, although it is likely that some resources will not be routinely documented in electronic format and data extraction from the medical notes will be supplemented by self-reported resource utilisation diaries filled out by the patients. Patients will be asked to complete the diaries for the period from weeks 0-12, 13-26 and every 13 weeks up to 152 weeks in which we will ask them to identify and record items relating to utilisation of any other relevant health care resources and patient burden, including time off work and foregone leisure and productivity time (i.e. absenteeism).

Where possible, we will value our items on health care resource utilisation using appropriate unit costs obtained from published sources, including the most recent version of Unit Costs of Health and Social Care and NHS Reference Costs. We will estimate unit costs which are not available from secondary sources using the approach used in the most recent version of Unit Costs of Health and Social Care.

Primary endpoint data will be collected within the trial. NICE recommends the use of preference-based health-related quality of life (HRQL) measures for the purpose of determining Quality Adjusted Life Years (QALYs) for economic evaluation. The use of quality-adjusted life years aims to capture the impact of disease progression and non-fatal events on quality of life in addition to any impact on survival. The EQ-5D-5L will be used to measure patient health-related QoL at baseline, 6 months, 12 months and annually thereafter. Patient's 5-dimension (mobility, self-care, usual activities, pain/discomfort, anxiety and depression) EQ-5D-5L health state classification at each trial time point will be converted into a utility score on a 0 to 1 scale where 0 is equivalent to dead, and 1, to perfect health. This conversion will be made using the new algorithm based on the UK value set currently being conducted by the EuroQol Group, if available

at the time of analysis. If not available the current crosswalk algorithm provided by the EuroQolgroup and algorithm estimated by Dolan et al. derived from a survey of the UK population (n=3337) [71], will be used. Utility values in the tariff set range from no problems on any of the five dimensions in the EQ-5D-5L descriptive system (value=1.0) to severe or extreme problems across all five dimensions (value=-0.594) [71, 72]. The utility scores will be combined with within-trial survival data to estimate the quality adjusted life-years (QALY's) required for the cost-utility analysis.

Adding an ARA to usual care in the CKD3b population may improve the patient's overall quality of life which goes beyond health. The ICEpop CAPability measure for Adults (ICECAP-A), and Quality of Life Visual Analogue Scale (QoL VAS ) will be used to measure CKD patient's overall quality of life, initially at baseline, 6 months, 12 months in a sub-population of the trial, and annually thereafter as funding permits. ICECAP-A is a self-reported measure of capability in adults (over 18 years). The measure covers attributes of wellbeing that were found to be important to adults in the UK. ICECAP-A comprises five attributes: settlement (feeling settled and secure), attachment (love, friendship and support), control (independence), role (achievement and progress), and enjoyment (enjoyment and pleasure); and each factor has four response levels. Index values have been estimated using a best-worst scaling technique. QoL VAS is a vertical line from 0 to 100 with anchors of best and worst imaginable life for people to report their perceived quality of life today. Together with KDQOL-SF and EQ-5D, ICECAP-A and QoL VAS will provide a full picture of treatment effect on CKD, general health and overall quality of life.

